## Introduction

Regional anesthesia has an extremely high safety profile [1]. However, complications related to regional techniques are reported in the literature such as local anesthetic toxicity, hematoma requiring medical attention or nerve injury [2–4]. Given that such complications are extremely rare their incidence is not fully known, mainly because it is estimated based on registry studies with an often limited sample size.

Moreover, while the cause-effect mechanism of regional anesthesia is clear for some complications – for instance, a pneumothorax following a paravertebral block –, the mechanism of action for other complications, such as nerve injury after regional anesthesia, is not well understood. Historically, it was believed that nerve injury resulted from the needle coming into direct contact with the nerve fibers, essentially causing mechanical trauma. Nevertheless, recent evidence challenges this view, showing that it is mechanically difficult to cause nerve injury solely through direct contact. In fact, nerve damage can occur even without any direct interaction with the nerve [5].

Thus, in addition to factors like local anesthetic toxicity, sub-perineural injection, high injection pressures within the epineurium, and sub-epineural hematoma resulting from forced contact between the needle and the nerve, other contributing factors may also play a role in nerve damage. These include altered coagulation profiles, the patient’s intrinsic fragility, possible comorbidities, and other currently unidentified factors [6].

The aim of the NEURAL study will be to provide a comprehensive estimate of the incidence of complications following regional anesthesia, with particular attention to nerve injury, hematoma, pneumothorax, and local anesthetic systemic toxicity (LAST). Moreover, by conducting a large multicenter prospective observational study, we will also seek to identify patient- and procedure-related risk factors that may predispose individuals to neurological or systemic adverse events. We hypothesize that the true incidence of complications is higher than currently appreciated from registry data, and that specific risk factors—including comorbidities, anticoagulant use, and technical variables related to block performance—contribute significantly to their occurrence.

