#### Accounting for center-level clustering.

Given the multicenter design of the NEURAL study, patients are clustered within participating institutions, and outcomes may be correlated due to shared clinical practices, operator expertise, equipment, or local protocols. To account for this hierarchical structure, multilevel (mixed-effects) regression models will be used for the primary and secondary analyses. Specifically, random-intercept logistic regression models will be applied to account for between-center variability when estimating associations between predictors and complications. The intraclass correlation coefficient (ICC) will be calculated to quantify the degree of clustering. As a sensitivity analysis, generalized estimating equations (GEE) with robust standard errors will also be considered.

All statistical analyses will be performed using R software. P-values < 0.05 will be considered indicative of statistical significance.

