### Sample size calculation

This is an observational study aimed at investigating very rare complications, the incidence of which is difficult to estimate. Literature reports an incidence ranging from 0 to 2.8%, depending on the study and cohort considered [8].

The sample size estimation was performed using an approach based on the precision of the proportion estimate, defined as the total width of the confidence interval. For this purpose, the Agresti-Coull Wilson method was applied [9].

Starting from a cumulative incidence of 0.005 (0.5%) [10], with a 95% confidence level and aiming for a confidence interval width of 0.003, a minimum of 3,396 subjects must be enrolled. The estimation was conducted using the {presize} package of R software, version 4.3.3 (2024-02-29 ucrt).

When the study was initially planned, we anticipated enrolling at least 10 centers in the NEURAL study, with an expected average recruitment of approximately 350 patients per center over two years, making the achievement of the planned sample size a realistic goal.

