### Strengths and limitations

A key strength of the NEURAL study lies in its multicenter, prospective, and observational design, coordinated under the auspices of SIAARTI. The inclusion of multiple tertiary centers across Italy ensures broad representation of clinical practice, patient demographics, and procedural variability, thereby enhancing the generalizability of results.

The study’s standardized definitions of complications and structured follow-up at 24 and 48 hours, as well as at 15 and 30 days—with extended follow-up up to one year for nerve injury—will enable accurate detection of both early and delayed complications. The detailed recording of procedural variables (e.g., ultrasound guidance, injection pressure, adjuvants used) and patient characteristics (e.g., comorbidities, anticoagulant use) allows for in-depth risk factor analysis using multivariable modeling.

However, the study also has inherent limitations. As an observational protocol, it cannot establish causal relationships between regional anesthesia and complications. Additionally, the identification of rare events may still be constrained by the sample size, despite careful power calculation. Potential variability in operator experience and institutional practices may introduce confounding, though standardized definitions and training across centers are intended to minimize this effect.

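### The center random intercept and its GEE check both mix within- and between-center contrasts, so odds ratios for block practices may carry center-level confounding

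*Protocol article*

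**What the plan says.** Under *Accounting for center-level clustering*, the protocol article fixes the model for risk factors: "random-intercept logistic regression models will be applied to account for between-center variability when estimating associations between predictors and complications". The reason it gives for clustering is that "outcomes may be correlated due to shared clinical practices, operator expertise, equipment, or local protocols". One check is named: "As a sensitivity analysis, generalized estimating equations (GEE) with robust standard errors will also be considered". No working correlation is stated.

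The candidate predictors in the data list under *Intraoperative time* include needle type and gauge, ultrasound use and approach, nerve stimulation, pressure limiter and adjuvants. The *Introduction* hypothesizes that risk factors including "technical variables related to block performance—contribute significantly to their occurrence". *Strengths and limitations* concedes that "Potential variability in operator experience and institutional practices may introduce confounding", and relies on common definitions and training to limit it. The article nowhere separates within-center from between-center effects, whether by center means, center fixed effects or conditional logistic regression.

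**The concern.** A random intercept estimates the within-center odds ratio without bias only if the center effect is unrelated to the predictor. The article attributes the center effect to practices, equipment and protocols, and these overlap with the predictors under study. A center that routinely uses a pressure limiter may also have more experienced operators, a different case mix, or closer surveillance for deficits.

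At stake is the reading of the risk-factor results. *Expected impact on clinical practice* looks forward to identifying modifiable risk factors and influencing device development. A practice with no effect could appear harmful or protective, depending on the sign of the correlation. Agreement between the random-intercept model and GEE would say little about it, because both are exposed to the same confounding.

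**Working it through.** **Inputs from the article.** Incidence 0.5% and N = 3,396 (*Sample size calculation*); 43 centers (*Recruitment*; 46 under *Ethical approval and protocol registration*); about 350 patients per center, an early figure for at least 10 centers over two years (*Sample size calculation*).

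**Assumptions, because the article gives none.** ICC on the latent scale, spread of practice use between centers (SD on the logit scale), and correlation between a center's use and its risk.

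**1. The plan's own figure.** The article says: "with a 95% confidence level and aiming for a confidence interval width of 0.003, a minimum of 3,396 subjects must be enrolled". The Agresti-Coull width is 2z√(p̃(1−p̃)/ñ), with ñ = n + z² and p̃ = (np + z²/2)/ñ. At n = 3,396, p = 0.005 and z = 1.96, ñ = 3,399.84, p̃ = (16.98 + 1.92)/3,399.84 = 0.00556 and the width is 0.0050. A width of 0.003 needs 8,853. This mismatch is a separate matter; only the event count is used here.

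**2. Events.** 3,396 × 0.005 = 17.0, and 17.0/43 = 0.39 per center. At 8,853 patients: 44 events, 1.0 per center. At 43 × 350 = 15,050: 75 events, 1.75 per center.

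**3. Mechanism.** The planned model is logit P = α + βx + u_j, with u_j independent of x. If u_j = γx̄_j + v_j, where x̄_j is the center's proportion of use, the fitted coefficient lies between β (within centers) and β + γ (between centers). Its position depends on how well each u_j is learned from the center's own data, roughly λ = σ²e/(1 + σ²e), where e is events per center. At ICC 0.10, σ² = (0.10/0.90) × π²/3 = 0.366.
- e = 0.39: λ ≈ 0.12
- e = 1.75: λ ≈ 0.39
- e = 100 (20,000 patients per center): λ ≈ 0.97

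So at the planned size the estimate is close to a pooled one.

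**4. Simulation, true odds ratio 1.** 43 equal centers, overall risk 0.5%. There were 300 simulated studies per row (150 at 350 per center, 60 at 20,000 per center). Cells are median odds ratios.

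| Patients per center | ICC | Correlation | SD of use | Random intercept | GEE exchangeable | GEE independence | With center proportion |
|---|---|---|---|---|---|---|---|
| 79 | 0.10 | 0 | 2 | 1.05 | 1.05 | 1.03 | 0.99 |
| 79 | 0.05 | −0.5 | 2 | 0.76 | 0.76 | 0.76 | 0.97 |
| 79 | 0.10 | −0.5 | 2 | 0.71 | 0.71 | 0.68 | 0.93 |
| 79 | 0.20 | −0.5 | 2 | 0.62 | 0.62 | 0.57 | 0.94 |
| 79 | 0.10 | −0.5 | 0.5 | 0.92 | 0.92 | 0.88 | 1.02 |
| 350 | 0.10 | −0.5 | 2 | 0.77 | 0.78 | 0.72 | 1.04 |
| 20,000 | 0.10 | −0.5 | 2 | 0.99 | 0.99 | 0.72 | 1.01 |

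With 300 runs the Monte Carlo error of a median is about 1.25 × 0.53/√300 = 0.04 on the log scale. The sign of the correlation sets only the direction: 1/0.71 = 1.41 and 1/0.77 = 1.30. Runs at +0.5 and ICC 0.10 gave 1.39 (79 per center) and 1.27 (350 per center) for the random intercept, against 0.90 and 0.96 with the center proportion. Center-stratified conditional logistic regression at +0.5 and 17 events gave 0.97 to 1.01. At correlation 0.3 the random intercept gave 1.11 to 1.25.

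**5. False-positive rate at 0.05.** At +0.5 and ICC 0.10, the random intercept rejects 7.5% of the time at 79 per center and 18% at 350. With the center proportion the rates are 5% and 6.5%.

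**The case against.** The strongest case against has five parts.

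- **The harm is conditional.** No figure in the article supports a correlation of 0.5. At zero there is no bias, and at 0.3 it is modest. This stands. A reader might infer that center quality will be reported as a device effect; the documents do not support that certainty.
- **More data and GEE are not powerless.** A reader might infer that no number of patients helps and that GEE removes nothing. Neither is right: with very large centers the random intercept and exchangeable GEE both reach 0.99, and only independence GEE stays at 0.72. At larger N, GEE can also visibly diverge from the random intercept. At feasible sizes, though, much of the bias remains. The 15,050-patient scenario is itself generous, since *Study duration* limits each center to six months.
- **The within-center estimate is not more accurate at the planned size.** Root mean square error at 17 events, ICC 0.10 and correlation 0.5 is 0.63 for the random intercept and 0.64 with the center proportion. This stands, and it rules out making the within-center odds ratio the headline estimate on grounds of accuracy.
- **The article is cautious.** Secondary analyses are called hypothesis-generating, causality is disclaimed, and the risk-factor analysis is a secondary objective. These caveats limit the harm, but they supply no analysis that could show the bias.
- **A random intercept with GEE is conventional, and details belong in a SAP.** The model is a reasonable default. But the article does name its clustering check, and that check is poorly suited to this particular threat.

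**Conclusion.** The point holds as a conditional weakness. The random-intercept model and GEE do not separate within-center from between-center contrasts, so odds ratios for practice-type predictors may carry center-level confounding, and the named check cannot reliably reveal it. With ICC 0.10, correlation 0.5 in either direction and wide variation in use, a null practice reads as about 1.3 to 1.4, or about 0.7 to 0.8 if the correlation is negative. Over ICC 0.05 to 0.20 at 17 events the range is 0.62 to 0.76 for the negative sign. The shift is negligible at zero correlation and small when use varies little between centers (0.92). All of these sizes rest on assumed values.

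A reader might also infer that the primary incidence estimate is affected, or that the random intercept must be replaced. Neither follows: the concern is with predictor associations only, and at 17 events the choice between the two estimates trades bias against variance.

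**What to change.** In *Accounting for center-level clustering*:

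1. Keep the random-intercept model.
2. For practice-type predictors that vary within centers, pre-specify a within-center sensitivity analysis: either the center's proportion of use as an added covariate, or center-stratified conditional logistic regression.
3. Report the within-center odds ratio beside the main one. Do not describe a practice as a modifiable risk factor when the two disagree materially, and define material disagreement in advance.
4. Keep GEE, if wanted, for population-averaged summaries.

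This needs no new data, and the article says that the study had not started at submission. The cost is precision: the standard error at 17 events is about 0.64 against 0.53 (0.64/0.53 = 1.21). The comparison of the two estimates is also noisy. By the usual approximation the standard error of their difference is √(0.64² − 0.53²) = 0.36, so at 17 events only about a two-fold gap (exp(1.96 × 0.36) = 2.0) stands clear of chance. Agreement should therefore not be read as proof of no confounding. No within-center estimate exists for a practice that does not vary within any center; such associations should be labelled as between-center only.

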### Statistical analysis

Data for each continuous variable will be analyzed to assess the normality of distribution using the Shapiro-Wilk test. Continuous variables with normal distributions will be reported as mean (standard deviation); those with non-normal distributions will be reported as median and interquartile range. Analysis of normally and non-normally distributed data will be performed using the two-tailed Student’s t-test and the Mann-Whitney U test, respectively.

If the proportion of missing data exceeds 5% for key variables, multiple imputation by chained equations will be performed under the assumption of missing at random. Imputation models will include all variables used in the primary analyses, including outcomes and relevant predictors. Sensitivity analyses will be conducted to compare complete-case analyses with imputed datasets. In addition, if differential loss to follow-up is observed, inverse probability weighting methods may be applied to assess the robustness of the findings. The amount of missing data and the methods used to address it will be transparently reported according to STROBE recommendations.

Results for categorical variables will be reported as numbers (percentages) and compared between groups using the chi-squared test or Fisher’s exact test, as appropriate.

To determine the strength and direction of association between two variables, the Bravais-Pearson correlation test will be used for variables with a normal distribution, and the Spearman rank correlation test for variables not meeting normal distribution assumptions.

To determine the relationships between the dependent categorical variable (e.g., complications) and one or more independent categorical variables (i.e., complication predictors), logistic regression will be performed to calculate odds ratios (OR) with 95% confidence intervals (CI). Given the anticipated low incidence of complications, rare-event bias may affect conventional maximum likelihood estimation. Therefore, penalized likelihood approaches—such as Firth’s bias-reduced logistic regression—will be used when appropriate to improve the stability and validity of parameter estimates. In cases of extremely sparse data, exact logistic regression methods may also be considered. Model adequacy will be assessed using goodness-of-fit statistics and calibration plots. The presence of multicollinearity will be assessed using variance inflation factors.

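### At the planned minimum of about 17 events, the robust-GEE sensitivity analysis gives false near-zero p-values for predictors with an event-free level; this affects uncommon predictors and needs one added rule

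*Protocol article*

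**What the plan says.** All statements are in the protocol article.

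- *Accounting for center-level clustering*: the main association model is fixed, in that "random-intercept logistic regression models will be applied to account for between-center variability when estimating associations between predictors and complications". It continues: "As a sensitivity analysis, generalized estimating equations (GEE) with robust standard errors will also be considered". The threshold is general: "P-values < 0.05 will be considered indicative of statistical significance".
- *Statistical analysis*: the sparse-data problem is recognised: "Given the anticipated low incidence of complications, rare-event bias may affect conventional maximum likelihood estimation". Firth's penalised logistic regression is offered when appropriate, and exact logistic regression is optional for extremely sparse data. Both are attached to the logistic regression; neither is carried over to the GEE. The same section calls secondary analyses hypothesis-generating, puts effect sizes and confidence intervals ahead of p-values, and allows false discovery rate control.
- *Sample size calculation*: the assumed incidence is 0.5%, and "aiming for a confidence interval width of 0.003, a minimum of 3,396 subjects must be enrolled".

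**The concern.** Where a predictor level has no event, its odds ratio cannot be estimated and an honest analysis says so. The robust (sandwich) variance does not. It is built from residuals, and in an event-free group the residuals shrink with the fitted risk, so the standard error stays small while the coefficient runs off to infinity.

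A sensitivity analysis exists to confirm or question the main result. Here it could mark a predictor as strongly protective (no event among the exposed) or as a strong risk factor (no event in the reference group) when the data say almost nothing. Uncommon predictors are most exposed. The article records peripheral and central neuropathy, adjuvant type and block type, and it wants risk factors for three regions, which leaves fewer events in each model.

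**Working it through.** **1. Event count.** 3,396 × 0.005 = 16.98, about 17. (The stated size itself does not reproduce. At 0.5%, an Agresti-Coull 95% interval of total width 0.003 needs 8,853 patients, and 3,396 fits a width of 0.005, which needs 3,395. That is a separate matter to reconcile; 8,853 patients would give about 44 events.)

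**2. Chance of an empty exposed group.** With exposure prevalence q and no effect, P(no exposed event | 17 events) = (1 − q)^17:

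| q | 2% | 5% | 10% | 20% | 30% |
|---|---|---|---|---|---|
| P(empty) | 71% | 42% | 17% | 2% | 0.2% |

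With 44 events and q = 5% it is 0.95^44, about 10%. With about 6 events, one third of 17 for a single region, it is 0.9^6 = 53% at 10% and 0.8^6 = 26% at 20%. Table 1 lists 51 blocks (13 + 18 + 20). If each of 17 events is attributed to one block, at least 51 − 17 = 34 blocks have none.

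**3. What GEE reports for an empty group.** Under independence working correlation, center k contributes about n₁ₖ/N₁ to the influence of the exposed group, where n₁ₖ is its number of exposed patients and N₁ their total. The fitted risk cancels. The sum of squares over K similar centers is about 1/K. The reference group adds about 1/(number of events). So

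SE ≈ √(1/43 + 1/17) = √(0.0233 + 0.0588) = 0.29.

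A standard GEE routine agreed. With 43 centers of 79 patients, 17 events, none exposed, and 5% exposure, the log odds ratio was about −22.3, the robust SE 0.27 to 0.31 and the printed p 0. The bias-reduced sandwich gave SE 0.27 to 0.32 and p = 0, so it is no repair. A model-based Wald test on data of this kind gave p of 0.98 or higher. With exchangeable correlation, 49 empty-cell datasets gave no finite p in 21 and p below 0.05 in the other 28 (largest 0.036).

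**4. False-positive rate with no true effect.** Assumptions: center SD 0.5 on the logit scale, independence GEE, two-sided robust Wald test at 5%, 3,000 simulated trials per setting. Repeat runs differed by about 2 percentage points.

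| Setting | 3% exposed | 5% | 10% | 20% |
|---|---|---|---|---|
| 43 centers × 79 | 64% | 47% | 21% | 7% |
| 10 centers × 340 | 66% | 48% | 24% | 8% |

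Every dataset with an empty cell was declared significant. With 43 centers the rate was about 4% to 5% at 30% and 50% exposure. When the reference group is the small one (90% exposed), it was 23% to 24%. In a region model with one third of the patients (about 6 events) it was 61% at 10% exposure and 36% at 20%. Fisher's exact test on null data of the same kind rejected in 2% to 4%.

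**5. Larger enrolment.** 43 × 350 = 15,050 patients, taking the article's average recruitment per center, gives about 14% at 3% exposure and 6% at 5%.

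**6. Effect of suppression.** Withholding GEE wherever a level has no event, and counting a withheld result as not significant, gives about 3% to 5% at 3% to 20% exposure with 43 centers.

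**The case against.** The strongest reply is about scope. GEE is only to be considered, and it stands behind a random-intercept model. Working correlation and small-sample corrections are details that an article may leave to the analysis plan. That stands, and their absence is not the point. The point is that the method named misbehaves at the event count planned, and that the safeguard in *Statistical analysis* is not tied to it.

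A second reply is that the article already urges caution, and that a log odds ratio of −22 is visible to anyone who looks at the two-by-two table. This is partly right. But stressing intervals does not help when the interval is as falsely narrow as the p-value, and false discovery rate control cannot remove p-values near 0. The article has no rule to withhold the result or say what replaces it.

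A third reply is that the prevalences and center SD are assumed, and that 17 events is a minimum the abstract expects to exceed. Both are correct, and they limit the size of the claim. Nothing in the article shows how common any particular predictor is.

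A reader might go further and infer that the robust GEE fails for every predictor, or that GEE must be replaced altogether. Neither is supported: rates are near nominal for common exposures, and withholding the zero-event results is enough.

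**Conclusion.** The concern holds, within limits. At about 17 events, robust GEE with independence working correlation returns a false near-zero p-value whenever a predictor level is event-free; the exchangeable form may fail instead. That matters for exposures of about 10% or less (or 90% or more), for single block types if they are analysed as predictors, and for region-specific models. The figures rest on the assumed center SD and prevalences, on equal center sizes in the 43 × 79 setting, and on GEE run in a Python routine and as a logistic fit with a center-cluster sandwich rather than in a dedicated R GEE package.

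It would be wrong to infer that the composite incidence estimate or the random-intercept model is invalidated. The harm is a sensitivity analysis that wrongly contradicts or appears to confirm the main model. It should be corrected, but it does not threaten the primary objective.

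**What to change.** Add to *Accounting for center-level clustering*: no robust GEE estimate, confidence interval or p-value is reported or interpreted for a predictor if any of its levels, exposed or reference, has zero events; Firth-penalised or exact inference that accounts for center (for example, a center-stratified exact conditional analysis) is used there. This extends the article's own sparse-data safeguard to the clustered analysis.

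The cost is a sentence of text and a few lines of code. Some uncommon predictors will have no GEE result, and their intervals will be slightly wider. A center-stratified exact analysis draws only on centers with events; with 17 events at least 43 − 17 = 26 of 43 centers have none.

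One limit remains. The 3% to 5% is an overall rate. Among datasets that still report a GEE result (43 centers), about 18% were significant at 2% exposure and 7% at 5%, against 3% at 10% and 20%. Surviving GEE results for very uncommon predictors still need to be read with the event counts beside them.
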